### Participants and recruitment

We will recruit 136 eligible patients with upper limb motor dysfunction caused by stroke from the rehabilitation hospitals affiliated to FJTCM. Eligible patients must meet the inclusion and exclusion criteria. A Standard Protocol Items: Recommendations for Interventional Trials (SPIRIT) Figure is shown in Fig. 2. Information about this trial will be available through the hospital website, and leaflets will be distributed to inpatients and outpatients at multiple locations in the hospital. Interested patients can contact the project leader through their therapists, among others, by telephone and e-mail. If an applicant meets the study criteria, then they will be invited to participate.

**Fig. 2 Fig2:**
[figure not shown]
A Standard Protocol Items: Recommendations for Interventional Trials (SPIRIT) Figure

### Inclusion criteria

Eligible patients are those (1) diagnosed with stroke and confirmed by computed tomography or magnetic resonance imaging; (2) first-ever clinical stroke occurred ≤ 6 months previously; (3) FMA-UE score of ≤ 33 points; (4) modified Ashworth score of grade II or lower; (5) aged between 18 and 80 years; (6) stable vital sign and consciousness; and (7) provided written informed consent to participate.

### Exclusion criteria

Criteria for exclusion are (1) upper limb dysfunction caused by brain tumor, brain trauma, and other diseases; (2) Montreal cognitive assessment score ≤ 26 points (if the education period is less than 12 years, then add 1 point to the score); (3) bone disease or joint damage causing limb deformities; (4) serious disease in the heart, liver, kidney, hematopoietic system, or endocrine system; and (5) participation in other clinical trials that may affect the results of this study.

### Withdrawal criteria and management

Participants will be allowed, or required, to withdraw from the trial based on (1) a major protocol violation; (2) development of a serious disease preventing continuation in the trial; (3) adverse events related to AT or MT; and (4) request to be withdrawn from the trial.

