## Methods

### Study design and setting

This trial will use a 2 × 2 factorial randomized controlled study to explore the clinical efficacy of AT combined with MT for improving the upper limb motor function of stroke patients. It will be performed in the Rehabilitation Hospitals Affiliated with Fujian University of Traditional Chinese Medicine (FJTCM). A total of 136 eligible subjects will be randomly divided into four groups, namely (1) AT group, (2) MT group, (3) combined treatment group (AT + MT), and (4) control group, in a 1:1:1:1 ratio. All subjects will receive conventional treatment, including health education and conventional medical therapy. The interventions will be performed 5 days per week for 4 weeks. AT, MT, and combined treatment (AT 15 min + MT 15 min) will be performed for 30 min per day. Therapists with more than 5 years of clinical experience will perform the interventions. A 4-week intervention and 12-week follow-up period will be conducted. Outcome measurements include the Fugl–Meyer Assessment for Upper Extremity (FMA-UE), Wolf Motor Function Test (WMFT), Visual Analogue Scale (VAS), Stroke Impact Scale (SIS), Modified Barthel Index (MBI), and adverse events. The flow diagram for this trial is presented in Fig. 1. The undertaking unit of this project (the Rehabilitation Hospitals Affiliated with FJTCM) and the ethics committees are responsible for making protocol decisions and for communicating important protocol modifications. In addition, the project undertaking unit is responsible for coordinating the work of all departments (e.g., trial registries, researcher training, informed consent of the participants, data management). If there are important protocol modifications, the project undertaking unit will notify relevant parties to convene a coordination meeting.

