### Sample size

Sample size was calculated based on the improvement in FMA-UE scores. Based on similar previous reports, the mean difference and SD were 42.86 ± 3.74 and 41.68 ± 3.44 for AT and conventional therapy, respectively [14]. We expect an effect size of at least 0.3 for outcomes after intervention. A sample size of 112 participants is required to sufficiently detect a target effect size with a type 1 error of 5% (α = 0.05) and 80% power (β = 0.20) by using Gpower 3.1.9.2 software. Considering a 20% attrition rate, a total of 136 participants are necessary, with 34 participants in each group.

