### Treatment allocation

The interventions will be performed 5 days per week for 4 weeks. AT and MT will be performed for 30 min per day, and combined treatment (AT 15 min + MT 15 min) will be performed for 30 min per day. During the study period, precise documentation of treatments, medication, and lifestyle-related influencing factors will be recorded in the case report forms (CRFs). All of the employees participating in this trial will receive standardized training regarding the study protocol, treatment methods, and assessments. The groups and intervention allocation are listed in Table 1.

**Table 1 Tab1:** Groups and intervention allocation

Groups	Interventions
Acupuncture treatment (AT) group	Conventional treatment + AT
Mirror therapy (MT) group	Conventional treatment + MT
Combination (AT + MT) group	Conventional treatment + AT + MT
Control group	Conventional treatment

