### Safety assessments

Acupuncture may cause discomfort or bruising at the sites of needle insertion, nausea, or feeling faint after each treatment. No adverse reactions caused by MT have been reported to date.

During the course of the study, any accidental injury and sudden illness will be recorded. The degree of symptoms, time of occurrence, duration, and treatment will be documented in the observation table. All adverse events reported should be analyzed regardless of the investigators’ assessments of causality. Serious adverse events will be reported to the ethics committee immediately.

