### Statistical analysis

All allocated subjects will be analyzed using the available data (i.e., on the basis of the intention-to-treat). A multiple imputation method will be used to complete missing data. Continuous variables will be expressed as mean (SD) for normal distribution or median for non-normal distribution, and categorical variables will be expressed as frequencies or percentages. A significance level of 95% (two-sided alpha *P* < 0.05) will be used.

After examining the data for normality (Kolmogorov–Smirnov test), the outcome measures will be analyzed using analysis of variance (assuming normal distribution) or Kruskal–Wallis (non-parametric). Demographic characteristics and other baseline values will be described using descriptive statistics for each group. Intragroup comparisons (changes in the FMA-UE, WMFT, VAS, SIS, and MBI scores before and after treatment) will be performed using the paired *t* test. The statistical significance of the observed differences between the groups will be assessed using 2 × 2 factorial analysis of variance to test the main effect and interaction effects of the two interventions (AT and MT). A statistician blinded to study groups will conduct statistical analysis.

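### Withdrawal for treatment-related adverse events is from the trial, not only the intervention, so outcomes can go missing for a reason that the control arm cannot have

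*Protocol article*

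**What the plan says.** In the protocol article, the section Withdrawal criteria and management opens: "Participants will be allowed, or required, to withdraw from the trial based on (1) a major protocol violation". Its other grounds are serious disease, the patient's own request, and "3) adverse events related to AT or MT". The section speaks of leaving the trial. It does not mention stopping the intervention as a separate step, and nothing elsewhere in the article says that a withdrawn patient is still assessed.

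Table 1, in Treatment allocation, gives the fourth arm as "Control group Conventional treatment", so controls receive neither AT nor MT. Safety assessments says of the needle treatment: "Acupuncture may cause discomfort or bruising at the sites of needle insertion, nausea, or feeling faint after each treatment". For MT it reports no known adverse reactions.

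Statistical analysis says: "All allocated subjects will be analyzed using the available data (i.e., on the basis of the intention-to-treat". It then adds: "A multiple imputation method will be used to complete missing data".

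Outcome assessment places the first measurement after baseline at the end of the 4-week intervention, with two further visits during follow-up. The Follow-up section says that all participants enter the 12-week follow-up, which a patient withdrawn from the trial cannot do.

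**The concern.** An intention-to-treat analysis needs outcomes on everyone randomised, whatever treatment they went on to receive. Here a patient who is willing to be measured may be required to leave. One of the grounds depends on having received AT or MT, so missing outcomes can be unequal between arms for a reason tied to treatment.

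No severity threshold is given for the adverse-event ground. Therapists and patients know the allocation, so the judgement that an event is related is made unblinded.

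Treatment runs only through weeks 1–4. A patient withdrawn in that period therefore has neither a Fugl–Meyer nor a Wolf Motor Function score after baseline. A standard imputation would have to fill in the values from baseline data and from patients who tolerated the treatment. If poor tolerance goes with poor recovery in ways that baseline does not show, the filled-in values are too good. The second aim, whether AT and MT alone or combined beat conventional treatment, is what is exposed.

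**Working it through.** **Inputs from the protocol article**
- Sample size: 42.86 (SD 3.74) for AT and 41.68 (SD 3.44) for conventional therapy; 34 per arm, 136 in all; 20% attrition overall, not split by arm or reason.
- Randomisation "in a 1:1:1:1 ratio"; the first assessment after baseline is at week 4.

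**Inputs assumed, because the article gives none**
- p, the excess share of an AT-containing arm withdrawn compared with control: 5–10%. In an arm of 34 that is 34 × 0.05 = 1.7 to 34 × 0.10 = 3.4 patients.
- D, how much worse those patients would have scored than the imputation model predicts: 0.5–1.0 SD.

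**Step 1: the planning difference.** Difference = 42.86 − 41.68 = 1.18 points. Pooled SD = √((3.74² + 3.44²)/2) = √12.91 = 3.59. Ratio = 1.18/3.59 = 0.328 SD. The article itself states: "We expect an effect size of at least 0.3 for outcomes after intervention". It does not name the type of effect size, so I use the derived 0.328 SD as the yardstick.

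**Step 2: the bias in one arm.** Let μ be the mean among patients who stay. The mean over everyone allocated is (1 − p)μ + p(μ − D) = μ − pD. If imputation centres the missing values at μ, the arm mean is overstated by pD. D is by definition the part that imputation misses, so the formula gives no result where imputation succeeds (D = 0).

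| p | D (SD) | p × D (SD) | Points (× 3.59) | Share of 0.328 SD |
|---|---|---|---|---|
| 5% | 0.5 | 0.025 | 0.09 | 8% |
| 5% | 1.0 | 0.05 | 0.18 | 15% |
| 10% | 0.5 | 0.05 | 0.18 | 15% |
| 10% | 1.0 | 0.10 | 0.36 | 30% |

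**Step 3: which contrasts carry it.** Write b = pD. If only AT causes such withdrawals, the AT and combined arms each shift by b. AT versus control is then biased by b, and so is the AT main effect, the average of (AT − control) and (combined − MT).

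The interaction is (combined − AT) − (MT − control).
- Only AT causes loss: (b − b) − (0 − 0) = 0.
- Losses from AT and MT add up: (2b − b) − (b − 0) = 0.
- Independent losses of 10% each: the combined arm loses 1 − 0.9² = 19%, so the bias is (0.19 − 0.10 − 0.10)D = −0.01D, that is −0.005 to −0.01 SD.
- All three active arms shift equally: (b − b) − (b − 0) = −b, which works against synergy.

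**Step 4: is lost power the issue?** Take AT and MT each as causing withdrawal with probability w, independently. At w = 5% the arms keep 34, 32.3, 32.3 and 30.7 patients, about 129 of 136; at w = 10%, about 123. For a 1-df effect, reading the 0.3 as Cohen's f (an assumption) at two-sided α = 0.05, the noncentral F gives power of 92% and 91%, against 93.5% with no loss. The cost is bias, not power.

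**The case against.** The strongest reply is that the analysis section already deals with this: everyone allocated is analysed and missing values are imputed. That stands as far as the analysis set goes. A reader might infer that violators are dropped and that the trial runs a per-protocol analysis under another name. The documents do not support this. The withdrawal section concerns participation, and no sentence removes anyone from the analysis. Analysing available data would omit withdrawn patients only if the imputation sentence that follows were ignored.

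Second, the rule is permissive as well as mandatory, so not every violator or every patient with an adverse event leaves. Violations, serious disease and patient request can occur in any arm; only the adverse-event ground is closed to controls. Both points stand.

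Third, an article condenses a fuller protocol, which may provide for assessment after withdrawal, and the imputation model belongs to the analysis plan. This stands in part. The finding is not that a detail is missing. The article states a rule, withdrawal from the trial that may be required, and that rule sits badly with its intention-to-treat claim and with its statement that all participants are followed up. That imputation assumes data missing at random is my assumption, not the article's.

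Fourth, a larger figure is tempting: 20% withdrawal with a 1.0 SD deficit gives 0.20 SD, or 61% of the planning difference. That would put the whole all-cause attrition allowance into excess loss in an active arm, together with the largest assumed deficit. The documents do not support it.

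A reader might also infer that safety records end at withdrawal, or that the synergy result is flattered. No passage says the first, and step 3 argues against the second.

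**Conclusion.** The point holds in a limited form. The article lets or makes patients leave the trial, not only the intervention, for a ground that controls cannot meet and that would fall mainly on the two AT-containing arms. What is lost is observed outcomes, including both primary scores after baseline for anyone withdrawn in weeks 1–4.

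Under the assumed ranges, comparisons of AT-containing arms with control are too favourable by 0.025–0.10 SD (0.09–0.36 points), about 8–30% of the difference used in planning. This requires that the patients concerned would have done worse in ways that the imputation model misses; if they would not, there is no bias. The article gives no withdrawal rates by arm or reason, so the figures show scale and are not an estimate. The interaction, which serves the first aim, is little affected if losses are additive. The change is worth making while recruitment continues, because outcomes not collected cannot be recovered at analysis.

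**What to change.** In Withdrawal criteria and management, separate stopping the study intervention from leaving the trial, and leave the clinical criteria for stopping treatment as they are. State that every randomised patient, including those with violations or treatment-related adverse events, is still assessed at week 4 and at both follow-up visits where able, unless consent is withdrawn. This also reconciles the section with Follow-up.

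In Statistical analysis, replace the reference to available data with, for example: all randomised participants are analysed in their allocated arm regardless of violations or treatment received; outcomes still missing are multiply imputed, with a delta-adjusted sensitivity analysis. The sensitivity analysis may already stand in an analysis plan that is not shown; its absence from the article is not itself a fault.

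The cost is a wording change and some extra effort to bring back the few patients who stop treatment, at visits already scheduled and with assessors already blinded.

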### Randomization and allocation

The randomization sequence will be created using SAS 9.1 by an independent statistician who works in the Evidence-Based Medicine Center of FJTCM. The allocation of participants will be concealed using envelopes that are sequentially numbered, opaque, and sealed. Competent doctors will work in strict accordance with the inclusion and exclusion criteria to determine whether the subjects can participate in the study. The investigator will then number the cases in chronological order. Screeners will assign the eligible number and opaque envelopes (containing random numbers and allocation and intervention information) to the therapists. The treating therapists will be notified of the allocation and make arrangements directly with the patient to administer the allocated treatment. Eligible participants will be informed of their group allocation by the project manager after their baseline information has been assessed. Researchers who determined the random numbers and performed the allocation will not participate in subject screening.

### Blinding

A single-blind method will be used. The outcome assessors, data manager, and statistics analyzer will evaluate the results of the study without being aware of subject allocation. The results of the assessment will be kept confidential to the investigator, thereby improving the accuracy of the test indicators, ensuring the effectiveness of the interventions, and assuring the objectivity and reliability of the evaluation. Certain staff will supervise the blind implementation process. The blind code will be disclosed after completion of the statistical analysis.

### Treatment allocation

The interventions will be performed 5 days per week for 4 weeks. AT and MT will be performed for 30 min per day, and combined treatment (AT 15 min + MT 15 min) will be performed for 30 min per day. During the study period, precise documentation of treatments, medication, and lifestyle-related influencing factors will be recorded in the case report forms (CRFs). All of the employees participating in this trial will receive standardized training regarding the study protocol, treatment methods, and assessments. The groups and intervention allocation are listed in Table 1.

**Table 1 Tab1:** Groups and intervention allocation

Groups	Interventions
Acupuncture treatment (AT) group	Conventional treatment + AT
Mirror therapy (MT) group	Conventional treatment + MT
Combination (AT + MT) group	Conventional treatment + AT + MT
Control group	Conventional treatment

### Conventional treatment

#### Basic treatment

All patients will receive conventional treatment provided by the rehabilitation hospitals affiliated to FJTCM. According to the *Chinese prevention and treatment guidelines of cerebrovascular disease* [15], the doctors will develop a basic treatment program based on the specific characteristics of individual patients. This means that patients will receive treatments deemed necessary by the doctors, such as conventional medical treatment, physical therapy, occupational therapy, and speech-language therapy, while receiving intervention. There are no restrictions for the aforementioned situations. We will track the types of interventions provided and precisely document the therapy treatments and medication.

#### Health education

We will use health education manuals to perform health education. The main contents of the manuals include (1) the severity of stroke to encourage people to focus enough attention and perform positive preventive measures actively; (2) the main risk and predisposing factors for stroke and secondary stroke prevention; and (3) management of and rehabilitation for stroke. For example, the manual describes when the best time to see the doctor is and how to cooperate with medical staff during treatment and rehabilitation.

### Mirror therapy

During initial treatment, the definition and content of MT will be explained to patients by an occupational therapist with more than 5 years of clinical experience. Patients will be instructed to sit close to a table on which a 35 × 35 cm mirror is vertically placed and then to put the upper limbs on the table. The contralateral upper limb will be positioned toward the reflective surface of the mirror, and the ipsilateral upper limb will be positioned on the opposite side of the mirror. Finally, patients will be required to observe the movement of the contralateral upper limbs in the mirror and to imagine the affected side in motion. Then, they will be required to perform the movement of the affected side as consistently as possible (if patients cannot complete the movement, then the experienced therapist will assist). Patients will need to complete six movements, namely shoulder flexion, elbow flexion and extension, forearm pronation, wrist flexion and extension, finger stretching, and thumb outreach. Patients will be asked to achieve a maximum range of motion for 30 min per day for 5 days per week for 4 weeks.

### AT protocol

Participants will be treated using five acupuncture points on the hemiplegia side (Jianyu [LI15], Quchi [LI11], Shou sanli [LI10], Hegu [LI4], and Waiguan [TE5]) by an acupuncturist with more than 5 years of clinical experience. AT will be performed with patients in the supine position. Points will be sterilized with alcohol, and the target position will then be fixed by the acupuncturist’s left hand. The acupuncturist’s right hand will insert the thin, disposable acupuncture needles (Huatuo, single use, 0.30 × 40 mm; Suzhou HuaTuo Medical Instruments, Suzhou, China).

The angle of insertion will be 10°–20° (between the needle and skin), and the needle depth will be approximately 1.0–1.5 B-cun. Following insertion, stimulation of the acupuncture point will be performed with bidirectional rotation of the needle sleeve at approximately 18–300 per min to achieve the sensation known as *Deqi*, which is commonly described as a glowing feeling.

The needle will be maintained in place for 30 min. A sterilized, dry cotton ball will be gently pressed against the point to prevent bleeding when each needle is withdrawn. The entire course of treatment will continue for 30 min per day for 5 days per week for 4 weeks.

### AT combined with MT

In the combined treatment group, patients will receive AT (15 min) and MT (15 min). However, the two treatments will be performed separately, yet the order of the two treatment methods will not be limited. Each treatment will last 15 min, for a total of 30 min per session.

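### The combined arm halves both sessions, so a null or negative 2 x 2 interaction cannot speak to AT-MT synergy at equal doses, and the main effects are not the effects of AT or MT

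*Protocol article*

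**What the plan says.** All places in the protocol article agree on the session lengths.

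- AT alone: "The needle will be maintained in place for 30 min" (AT protocol).
- MT alone: "Patients will be asked to achieve a maximum range of motion for 30 min per day for 5 days per week for 4 weeks" (Mirror therapy).
- Combined arm: "In the combined treatment group, patients will receive AT (15 min) and MT (15 min"), and "Each treatment will last 15 min, for a total of 30 min per session" (both AT combined with MT); likewise "combined treatment (AT 15 min + MT 15 min) will be performed for 30 min per day" (Treatment allocation). The Abstract and Study design and setting say the same.
- Table 1 nevertheless labels the combined arm "Conventional treatment + AT + MT", as if each component were the same thing as in its own arm.

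The Background hypothesises that the two therapies together achieve more than their separate effects added up. It makes synergy the first aim, and the comparison of AT, MT and the combination with conventional treatment the second. Statistical analysis plans a "factorial analysis of variance to test the main effect and interaction effects of the two interventions (AT and MT"). It also says that "the outcome measures will be analyzed using analysis of variance (assuming normal distribution"), with Kruskal-Wallis as the non-parametric alternative. The limitations in the Discussion mention the lack of double blinding and of long-term follow-up, but not the split session.

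**The concern.** A 2 x 2 interaction measures departure from additivity only if each factor is at the same level wherever it is present. Here, AT present means 30 minutes in one arm and 15 in another, and likewise for MT. The interaction is the test of the first aim. It compares one split 15+15 minute session with the sum of two 30-minute sessions. If 15 minutes achieves less than 30, purely additive therapies produce a negative interaction, and real synergy can be cancelled out. A reader of the trial report could then be told that the therapies do not act together, or that they interfere, only because each was given for half the time. The main effects, which would naturally be read as the effects of AT and of MT, carry the same problem into the second aim.

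**Working it through.** **The plan's own figures.** Sample size gives an effect size of 0.3, 112 participants and 136 after attrition. Read as Cohen's f with four groups, 0.3 gives 111, or 112 in equal groups, when the numerator has 2 degrees of freedom (a 1-df effect, as in a 2 x 2 design, needs 90). The argument below does not depend on this. It uses only 112/4 = 28 analysed per arm.

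**Minutes per day (AT/MT).** Control 0/0; AT 30/0; MT 0/30; combined 15/15.

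**Model (SD units, relative to control).** Let a and m be the 30-minute effects, gA and gM the shares of them kept at 15 minutes, and s the synergy at the delivered doses.

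- AT arm: a. MT arm: m. Combined arm: gA·a + gM·m + s.
- Interaction = combined − AT − MT + control = s − (1 − gA)a − (1 − gM)m.

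There is no 15-minute single-therapy arm, so no model fitted to these four means can separate s from the lost-dose terms.

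**Main effect of AT.** ½[(AT − control) + (combined − MT)] = [(1 + gA)a − (1 − gM)m + s]/2. The second term is there because combined minus MT alone adds 15 minutes of AT and also removes 15 minutes of MT. Two examples with s = 0 and both shares 0.5:

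- a = m = 0.6: main effect (0.90 − 0.30)/2 = 0.30. The 30-minute effect is 0.60, and the average over the two session lengths is (0.60 + 0.30)/2 = 0.45.
- a = 0.2, m = 0.6: main effect (0.30 − 0.30)/2 = 0, although AT works at both lengths (0.20 and 0.10).

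The same holds for MT with the letters exchanged.

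**Inputs for size (assumptions, since the protocol gives no dose-response).** Take a = m = d and gA = gM = g.

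- d = 0.33: from the earlier report in Sample size, (42.86 − 41.68)/√[(3.74² + 3.44²)/2] = 1.18/3.593 = 0.328, assumed equal for MT.
- d = 0.6: 2 × 0.3, if 0.3 is Cohen's f for a two-level factor.
- Interaction standard error 2/√28 = 0.378; df = 112 − 4 = 108; critical t = 1.982; 95% CI half-width 1.982 × 0.378 = 0.75 SD.

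The probabilities come from the noncentral t with noncentrality (interaction/0.378). The synergy benchmark is s = 1.2 SD, which is f = 0.3 on the interaction (4 × 0.3).

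| d | g | Interaction if s = 0 | P(significant negative), s = 0 | P(significant positive), s = 1.2 |
|---|---|---|---|---|
| either | 1 | 0 | 2.5% | 88% |
| 0.33 | 0.9 | −0.07 | 3.7% | 84% |
| 0.33 | 0.75 | −0.16 | 6.3% | 78% |
| 0.33 | 0.5 | −0.33 | 13.6% | 63% |
| 0.6 | 0.9 | −0.12 | 5.0% | 81% |
| 0.6 | 0.75 | −0.30 | 12.0% | 66% |
| 0.6 | 0.5 | −0.60 | 35.0% | 35% |

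**The case against.** The split session is disclosed consistently and looks deliberate: matching total time at 30 minutes makes combined versus AT and combined versus MT fair comparisons. The Background does not promise equal component doses, and nothing in the protocol says that a null or negative interaction will be reported as antagonism. All of this is right. It defends the regimen, but it does not make the interaction a test against the sum of two 30-minute effects at matched doses.

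A reader might infer that any claim of synergy from this trial would be unsafe. The documents do not support that. If shorter sessions work no better than longer ones, the lost-dose terms can only pull the interaction down, so a significantly positive result, the hypothesised direction, stays valid and false synergy is not made more likely.

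A reader might also infer that equal doses would have made a null informative. They would not: the half-width is 0.75 SD even at g = 1, where power is 35% for a synergy of 0.6 SD and 14% for 0.33 SD. At d = 0.33 the dose shift is below one standard error for every g shown. Imprecision is a separate limit, and the dose difference adds to it.

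Finally, the 35% figure needs d = 0.6 for both therapies and half of each effect lost. It is the upper end of an assumed range, not an expected rate. A synergy of 1.2 SD is also a very large benchmark: at d = 0.6 and g = 1 it means a combined effect of 2.4 SD over control.

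**Conclusion.** The point stands, limited to what a null or negative interaction, and the factorial main effects, can be said to show. That the interaction mixes synergy with lost dose follows from the stated minutes alone and needs no assumption; an analysis plan working on these four arms could not undo it. How much this matters depends on the share of effect kept at 15 minutes, which the documents do not give. If 15 minutes works as well as 30, the shift is zero. With shares of 0.9 to 0.5, the rate of spurious antagonism runs from 3.7% to 13.6% at d = 0.33 and from 5.0% to 35.0% at d = 0.6. Power for a 1.2 SD synergy falls from 88% to 63% and 35% respectively at a share of 0.5.

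It would be tempting to describe the main effects as averages over the two session lengths. They are not that either, as the derivation shows. The four-group ANOVA or Kruskal-Wallis test remains valid for the regimens as delivered, but it does not test synergy.

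**What to change.** Arms, visits and sample size stay as they are.

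1. In the aims (end of Background) and in Statistical analysis, state that the interaction compares a split 15+15 minute session with the sum of two 30-minute sessions.
2. Let only a significantly positive interaction support super-additivity, under the written assumption that shorter sessions work no better than longer ones.
3. Draw no conclusion of no synergy, or of antagonism, at equal doses from a null or negative interaction; read it as applying to the split regimen as delivered.
4. Do not interpret the factorial main effects as the effects of AT or MT. Answer the second aim with contrasts of AT, MT and combined, each against control, from the four-arm model with 95% confidence intervals. Report the time-matched combined versus AT and combined versus MT contrasts as supportive.

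The cost is wording and a few contrasts from the same data, which can be added while recruitment continues. The real downside is precision. A pairwise contrast at 28 per arm has a half-width of 1.982 × √(2/28) = 0.53 SD, against 1.982 × √(2/56) = 0.37 SD for a factorial main effect. The main effect is tighter, but it estimates the wrong quantity for the second aim.
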